#### **6.5.3 Non-serious AEs**

All adverse events should be recorded in the relevant CRF and submitted to SCTU.

#### **6.5.4 Pre-existing Conditions**

Medically significant pre-existing conditions (those which are present prior to informed consent) should not be reported as an AE unless the conditions worsens during the trial. The condition, however, must be reported on the Baseline CRF. Any adverse events which occur after informed consent taken should be recorded on the AE CRF as per safety reporting section.

#### **6.5.5 Serious Adverse Events**

All SAEs should be reported within 24 hours of the local site becoming aware of the event. The SAE Non-CTIMP Form asks for nature of event, date of onset, severity, corrective therapies given, outcome, causality (i.e. unrelated, unlikely, possible, probably, definitely) and expectedness. The responsible investigator should assign the causality and expectedness of the event with reference to the events listed in Section 6.4.1. The event term should be in accordance with the latest version of MedDRA and grades given in accordance with the NCI CTCAE v5, Additional information should be provided as soon as possible if the event has not resolved at the time of reporting.

### **6.6 SCTU RESPONSIBILITIES FOR SAFETY REPORTING TO REC**

SCTU will notify the necessary competent authorities of all **Related and Unexpected** SAEs occurring during the study within 15 days.

SCTU submit all safety information to the REC in annual progress report.

## **7 STATISTICS AND DATA ANALYSES**

### **7.1 SAMPLE SIZE**

It is expected that the intervention development will require approximately 20 participants. This number is based on cycles of 4-6 patients with up to 4 iterative cycles. This figure is based on previous experience of the Chief Investigator from a similar trial where a more complex intervention was developed (14).

Feasibility data analysis will be descriptive: recruitment rates, participant characteristics, acceptability of trial procedures and process variables.

## **7.2 QUALITATIVE INTERVIEWS**

Qualitative interviews with participants and healthcare professionals will explore perceptions and experiences of the intervention and how it might be improved. Treatment fidelity will be maintained by including all content to be covered on checklists, assessed by intervention access/usage and examining any diversions from the protocol.

Data analysis will commence as soon as data collection begins. Meetings will be held between the team to discuss preliminary findings, make refinements to the topic guides if required and to agree on a coding frame. A thematic approach will be used to analyse the data, the purpose of which is to look for, and understand, patterns and experiences which cut across different people's accounts and the reasons for these. Key aspects of the analysis will include: (a) comparisons between participants' interviews to identify differences in their perceptions, experiences and behaviours, and the reasons for these; (b) comparison of participant and health professional accounts to identify similarities and differences in their understandings and any potential impact on diabetes self-management practices; (c) cross-comparison of participants' accounts to identify common issues and experiences as well differences between subgroups of participants (e.g. men versus women, participants of different ages etc.), and the reasons for these.

The interviews will also explore participants' information and support needs and whether, and in what ways, the intervention and follow-up care could be changed or improved.

### **7.2.1 Quality procedures**

Several quality procedures will be used to increase the validity and credibility. Procedures to be used are for instance: using a member check, the use of several data collection methods (triangulation), using a reflexive diary, doing the analyses by two researchers and the use of 'thick descriptions'.

## **8 REGULATORY**

### **8.1 CLINICAL TRIAL AUTHORISATION**

This study is not considered to be a clinical trial of a medicinal product, so clinical trial authorisation from the UK Competent Authority the Medicines and Healthcare products Regulatory Agency (MHRA) is not applicable.

## **9 ETHICAL CONSIDERATIONS**

The study will be conducted in accordance with the recommendations for physicians involved in research on human participants adopted by the 18th World Medical Assembly, Helsinki 1964 as revised and recognised by governing laws and EU Directives. Each participant's consent to participate in the study should be obtained after a full explanation has been given of treatment options, including the conventional and generally accepted methods of treatment. The right of the participant to refuse to participate in the study without giving reasons must be respected.

After the participant has entered the study, the clinician may give alternative treatment to that specified in the protocol, at any stage, if they feel it to be in the best interest of the

participant. However, reasons for doing so should be recorded and the participant will remain within the study for the purpose of follow-up and data analysis according to the treatment option to which they have been allocated. Similarly, the participant remains free to withdraw at any time from protocol treatment and study follow-up without giving reasons and without prejudicing their further treatment.

## **9.1 SPECIFIC ETHICAL CONSIDERATIONS**

Our proposal to randomise patients on the same day as the decision to proceed to surgery is made may prove controversial. However, it is believed that this is entirely justified as (i) this is a pragmatic approach, which reflects how the intervention would be used in routine practice, (ii) it is more convenient for patients, relieving them on an additional journey to a potentially remote hospital, and (iii) this approach to consent has been used previously within the European Union (12). All patients will have an opportunity to discuss the study face-to-face with a clinician before randomisation, and will of course be able to withdraw should they change their mind.

Participants will be reassured that all personally identifiable data collected during the course of the research will be kept strictly confidential, and non-identifiable data will be shared in accordance with the University of Southampton policies. All patient data will be anonymised and stored on a database in accordance with current Data Protection Regulations. We will also seek the patient's permission to inform their general practitioner that they are taking part in this study. Documentation relating to clinical trials managed by Southampton CTU is retained for 15 years after notification of the trial's end.

## **9.2 ETHICAL APPROVAL**

The study protocol has received the favourable opinion of a Research Ethics Committee or Institutional Review Board (IRB) in the approved national participating countries.

## **9.3 INFORMED CONSENT PROCESS**

Informed consent is a process that is initiated prior to an individual agreeing to participate in a study and continues throughout the individual's participation. In obtaining and documenting informed consent, the investigator should comply with applicable regulatory requirements and should adhere to the principles of GCP.

Discussion of objectives, risks and inconveniences of the study and the conditions under which it is to be conducted are to be provided to the participant by appropriately delegated staff with knowledge in obtaining informed consent with reference to the patient information leaflet. This information will emphasise that participation in the trial is voluntary and that the participant may withdraw from the trial at any time and for any reason. The participant will be given the opportunity to ask any questions that may arise and provided the opportunity to discuss the study with family members, friend or an independent healthcare professional outside of the research team and time to consider the information prior to agreeing to participate.

## **9.4 CONFIDENTIALITY**

SCTU will preserve the confidentiality of participants taking part in the study. The investigator must ensure that participant's anonymity will be maintained and that their identities are protected from unauthorised parties. On CRFs participants will not be identified by their names, but by an identification code.

## **10 SPONSOR**

SCTU, Chief Investigator and other appropriate organisations have been delegated specific duties by the Sponsor and this is documented in the trial task allocation matrix.

The duties assigned to the study sites (NHS Trusts or others taking part in this study) are detailed in the Non-Commercial Agreement.

### **10.1 INDEMNITY**

For NHS sponsored research HSG (96) 48 reference no.2 applies. If there is negligent harm during the clinical study when the NHS body owes a duty of care to the person harmed, NHS Indemnity covers NHS staff, medical academic staff with honorary contracts, and those conducting the study. NHS Indemnity does not offer no-fault compensation and is unable to agree in advance to pay compensation for non-negligent harm. Ex-gratia payments may be considered in the case of a claim.

### **10.2 FUNDING**

This study is funded by the National Institute for Health Research Health Technology Assessment Programme.

#### **10.2.1 Site payments**

The payments assigned to the study sites (NHS Trusts or others taking part in this study) are detailed in the Non-Commercial Agreement.

This study is automatically eligible for the NIHR portfolio. This enables Trusts to apply to their comprehensive local research network for service support costs, if required.

#### **10.2.2 Participant payments**

Participants will not be paid for participation in this study.

### **10.3 AUDITS AND INSPECTIONS**

The study may be participant to inspection and audit by UHS (under their remit as Sponsor), SCTU (as the Sponsor's delegate) and other regulatory bodies to ensure adherence to the principles of GCP, Research Governance Framework for Health and Social Care, applicable contracts/agreements and national regulations.

## **11 STUDY OVERSIGHT GROUPS**

The day-to-day management of the trial will be co-ordinated through the SCTU and oversight will be maintained by the Trial Management Group, the Trial Steering Committee and the Data Monitoring and Ethics Committee.

### **11.1 TRIAL MANAGEMENT GROUP (TMG)**

The TMG is responsible for overseeing progress of the study, including both the clinical and practical aspects. The Chair of the TMG will be the Chief Investigator of the study.

The OCTOPuS TMG charter defines the membership, terms of reference, roles, responsibilities, authority, decision-making and relationships of the TMG, including the timing of meetings, frequency and format of meetings and relationships with other trial committees.

## **11.2 TRIAL STEERING COMMITTEE (TSC)**

The TSC act as the oversight body on behalf of the Sponsor and Funder. The TSC will meet in person at least yearly and have at least one further teleconference meeting during the year. The majority of members of the TSC, including the Chair, should be independent of the study.

The OCTOPuS TSC charter defines the membership, terms of reference, roles, responsibilities, authority, decision-making and relationships of the TSC, including the timing of meetings, frequency and format of meetings and relationships with other trial committees.

## **12 DATA MANAGEMENT**

Participant data will be entered onto paper CRF and sent to Southampton CTU retained in accordance with current Data Protection Regulations. The PI is responsible for ensuring the accuracy, completeness, and timeliness of the data entered and that each CRF is signed.

The participant data is pseudo anonymised by assigning each participant a participant identifier code which is used to identify the participant during the study and for any participant- specific clarification between SCTU and site. The site retains a participant identification code list which is only available to site staff.

The Informed Consent Form will specify the participant data to be collected and how it will be managed or might be shared; including handling of all Patient Identifiable Data (PID) and sensitive PID adhering to relevant data protection law.

Only the Investigator and personnel authorised by them should enter or change data in the CRFs. When requested, laboratory data must be transcribed, with all investigator observations entered into the CRF. The original laboratory reports must be retained by the Investigator for future reference.

A Data Management Plan (DMP) providing full details of the study specific data management strategy for the trial will be available and a Trial Schedule with planned and actual milestones, CRF tracking and central monitoring for active trial management created.

Data queries will be manually raised by the study team, if required.

At the end of the study after all queries have been resolved, the PI will confirm the data integrity by signing the appropriate CRF. The CRFs will be archived according to SCTU policy.

Data may be requested from the Data Access Committee at SCTU. Request will be considered on a monthly basis.

## **13 MONITORING**

### **13.1 CENTRAL MONITORING**

Data stored at SCTU will be checked for missing or unusual values (range checks) and checked for consistency within participants over time. Any suspect data will be returned to the site in the form of data queries. Data query forms will be produced at SCTU from the trial database and sent either electronically or through the post to a named individual (as listed on the site delegation log). Sites will respond to the queries providing an explanation/resolution to the discrepancies and return the data query forms to SCTU. The forms will then be filed along with the appropriate CRFs and the appropriate corrections made on the database. There are a number of monitoring features in place at SCTU to ensure reliability and validity of the trial data, which are detailed in the trial monitoring plan.

### **13.2 CLINICAL SITE MONITORING**

Monitoring will be completed as per the trial monitoring plan. However, it is not expected that there will be any onsite monitoring as part of the intervention development.

#### **13.2.1 Source Data Verification**

On receipt of a written request from SCTU, the PI will allow the SCTU direct access to relevant source documentation for verification (taking into account data protection regulations). Access should also be given to study staff and departments (e.g. pharmacy).

The participants' medical records and other relevant data may also be reviewed by appropriate qualified personnel independent from the SCTU appointed to audit the study, including representatives of the Competent Authority. Details will remain confidential and participants' names will not be recorded outside the study site.

### **13.3 SOURCE DATA**

Source documents are where data are first recorded, and from which participants' CRF data are obtained. These include, but are not limited to, hospital records (from which medical history and previous and concurrent medication may be summarised), clinical and office charts, laboratory and pharmacy records, diaries, microfiches, radiographs, and correspondence.

## **14 RECORD RETENTION AND ARCHIVING**

Trial documents will be retained in a secure location during and after the trial has finished.

The PI or delegate must maintain adequate and accurate records to enable the conduct of the study to be fully documented and the study data to be subsequently verified. After study closure the PI will maintain all source documents and study related documents. All source documents will be retained for a period of 15 years following the end of the study.

Sites are responsible for archiving the ISF and participant's medical records.

The Sponsor is responsible for archiving the TMF and other relevant documentation.

## **15 PUBLICATION POLICY**

Data from all centres will be analysed together and published as soon as possible.

Individual investigators may not publish data concerning their patients that are directly relevant to questions posed by the trial until the Trial Management Group (TMG) has published its report. The TMG will form the basis of the Writing Committee and advise on the nature of publications. All publications shall include a list of investigators, and if there are named authors, these should include the Chief Investigator, Co-Investigators, Trial Manager, and Statistician(s) involved in the trial. Named authors will be agreed by the CI and Director of SCTU. If there are no named authors then a 'writing committee' will be identified.

## 17 APPENDICES

### 17.1 APPENDIX 1- PROGRESS GRADING

Table 1 – Actions to be taken depending on progress grade

| Grade        | Action                                                                                                                                                                                                         |
|--------------|----------------------------------------------------------------------------------------------------------------------------------------------------------------------------------------------------------------|
| Green | Continue trial, keeping an eye on accrual.                                                                                                                                                                     |
| Amber | Working with governance committees (TSC, TMG, PPI Committees), seek root cause for under performance. Consider whether these can be mitigated through work with organisations or individuals within the study. |
| Red   | Review the study with governance committees, taking steps as detailed under amber, but also explicitly considering recommending study closure.                                                                 |

**Table 2 - Progress grading time points and criteria**

| Assessment Point                                                            | Green                                                                                                                                                                                                                                                                                    | Amber                                                                                                                                                                                                   | Red                                                                                                                                                                                                          |
|------------------------------------------------------------------------------------|-------------------------------------------------------------------------------------------------------------------------------------------------------------------------------------------------------------------------------------------------------------------------------------------------|----------------------------------------------------------------------------------------------------------------------------------------------------------------------------------------------------------------|---------------------------------------------------------------------------------------------------------------------------------------------------------------------------------------------------------------------|
| After 100 patients have had surgery (50 intervention and 50 control) | HbA 1c reduction in intervention group > 5mmol/mol                                                                                                                                                                                                                                   | HbA 1c reduction in intervention group < 5mmol/mol                                                                                                                                                  | HbA 1c reduction in intervention group not consistent with physiological effect                                                                                                                          |
| 6 complete months after 1st recruiting site has opened               | >= 8 centres have recruited at least one patient and
>= 50 patients have been recruited and
At least 10 patients have completed their OCTOPuS intervention and have either received surgery, or have had their surgery cancelled or postponed for either clinical or operational reasons. | One or two criteria in green column met                                                                                                                                                                        | No criteria in green column met                                                                                                                                                                                     |
| 12 complete months after 1st recruiting site has opened              | >= 12 centres have recruited at least one patient and
and
At least 50 patients have completed their OCTOPuS intervention and have either received surgery, or have had their surgery cancelled or postponed for either clinical or operational reasons.                                   | Only one criterion from green column met                                                                                                                                                                       | No criteria on green column met                                                                                                                                                                                     |
| End of month 15 of recruitment                                       | The mean recruitment rate across the trial in months 13, 14, and 15 following the opening of the first recruiting centre is compatible with completing recruitment by the end of month 27 of recruitment                                                                                        | The mean recruitment rate across the trial in months 13, 14, and 15 following the opening of the first recruiting centre is compatible with achieving 75% or more of target recruitment by the end of month 27 | The mean recruitment rate across the trial in months 13, 14, and 15 following the opening of the first recruiting centre is not compatible with achieving at least 75% of target recruitment by the end of month 27 |

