### **2.1.5 Progression rules for moving to main trial**

If a manualised intervention and associated training package cannot be provided, which is acceptable to patients, it will be impossible to deliver the main study. The TSC will review a report of stage 1 from the Trial Management Group, and make a recommendation to stop or proceed.

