## **3 STUDY DESIGN**

A single centre, feasibility study to develop an outpatient manualised intervention and associated training package, which is acceptable to people with sub-optimally controlled type 1 or type 2 diabetes undergoing elective cardiothoracic surgery and health professionals.

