### **3.1 PRIMARY ENDPOINT**

To produce a manualised intervention and associated training package, which is acceptable to patients and their healthcare professionals that can be used in a multicentre randomised controlled trial involving at least 8 cardiothoracic centres across the UK.

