#### **5.5.1 *Reasons for study discontinuation***

Participants may be discontinued from the study in the event of:

- Clinical decision, as judged by the Principal Investigator or Chief Investigator
- In the event the trial is discontinued due to the interim analysis (as outlined in Section 7.3)

Full details of the reason for study discontinuation should be recorded in the eCRF and medical record.

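### Appendix 1 grades a multicentre randomised trial: at three of its four checkpoints this single-centre study of about 20 cannot reach Green or cannot be assessed, and Section 5.5.1 cites an interim analysis that does not exist

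*Protocol*

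**What the plan says.** Section 3 of the protocol describes "A single centre, feasibility study to develop an outpatient manualised intervention and associated training package". The synopsis gives one site and a sample size of 20-30. Section 7.1 expects about 20 participants, from cycles of 4-6 patients and up to four cycles. Section 4.5 gives each participant a sequential ID and describes no allocation to groups. Section 2 sets a nine-month development period.

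Appendix 1 (17.1) has two tables. Table 1 ties each grade to an action; Red means a review with the governance committees, "but also explicitly considering recommending study closure". Table 2 has four assessment points:

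- an HbA1c check, "After 100 patients have had surgery (50 intervention and 50 control" arm patients;
- 6 months after the first site opens: at least 8 recruiting centres, at least 50 recruited, and at least 10 who have completed the intervention and either had surgery or had it cancelled or postponed;
- 12 months: at least "12 centres have recruited at least one patient", and at least 50 such completers;
- the end of month 15: a recruitment rate that would reach target by month 27.

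Section 5.5.1 lists as a reason for discontinuing participants: "In the event the trial is discontinued due to the interim analysis (as outlined in Section 7.3". Section 7 contains only 7.1, 7.2 and 7.2.1.

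Section 2.1.5 leaves the stop-or-proceed recommendation to the TSC. It says that without a manual and training package "which is acceptable to patients, it will be impossible to deliver the main study". The primary endpoint in 3.1 is wider: "acceptable to patients and their healthcare professionals".

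**The concern.** Appendix 1 is current text, appears in the contents list, and is not marked as applying only to the later randomised trial. It holds the only numeric progress thresholds in the protocol. A committee that opened it to grade this study would be using centre counts, patient numbers and a control arm that the study does not have. Most of the resulting grades would reflect the design and say little about how the study had gone. One of them would prompt a discussion of closure.

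The 5.5.1 clause is the same kind of fault: a stated ground for discontinuation that points to an analysis described nowhere.

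**Working it through.** **Inputs.** Centres: 1 (synopsis, Section 3). Control patients: 0 (4.5; no control group is described). Some sections, such as 9.1, still speak of randomisation, but none gives an allocation procedure. Participants: about 20 (7.1) or 20-30 (synopsis).

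**The plan's own sample size.** 4 cycles x 5 patients = 20, which agrees with 7.1. Section 2 gives 3-4 cycles of 4-6, so the range is 3 x 4 = 12 to 4 x 6 = 24. The check below uses N from 12 to 30, to cover the synopsis as well.

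**Each row of Table 2 against those inputs.**

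| Row | Printed Green requirement or trigger | Attainable here | Result |
|---|---|---|---|
| HbA1c | 100 operated, 50 of them control | at most 30 operated, 0 control | never assessed |
| 6 months | 8 centres; 50 recruited; 10 completers | 1 < 8; 30 < 50; 10 possible | at most 1 of 3: Amber with 10 or more completers, otherwise Red |
| 12 months | 12 centres; 50 completers | 1 < 12; 30 < 50 | 0 of 2: Red for every N from 12 to 30 |
| Month 15 | rate compatible with reaching target by month 27 | depends on target | Green possible |

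**Month 15 in detail.** Take T as the target and r as the number recruited by month 12. A constant rate over months 13 to 27 (15 months) must be at least (T - r)/15 for Green.

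- T = 20, r = 12 (an assumption): 8/15 = 0.53 per month.
- T = 20, r = 0: 20/15 = 1.33 per month.
- T = 30, r = 0: 30/15 = 2.0 per month.
- If recruitment is already complete: 0.

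The row needs no minimum number of centres or patients and no control arm. Its fault is the horizon: month 27 against a nine-month development period.

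**Will month 12 be reached?** The documents do not settle this. Nine months is the development period; under 3.3 the study ends after the last interview. Suppose the cycles run one after another, each taking about 12 weeks, with interviews up to 6 weeks after surgery. Three cycles then take 3 x 12 + 6 = 42 weeks, and four take 4 x 12 + 6 = 54 weeks. Overlapping cycles would shorten this. On the same assumption two cycles, 8 to 12 people, finish within the first 6 months, so even the 10 completers needed for Amber are not assured.

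**Section 7.3.** Both the contents list and the text of Section 7 stop at 7.2 and its subsection. No interim analysis is described elsewhere.

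**Section 2.1.5 beside 1.2 and 3.1.** Section 2.1.5 names patients only. Section 1.2 and the synopsis rationale make acceptability to both patients and staff the condition for the randomised trial, and 3.1 includes both in the endpoint.

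**The case against.** The strongest reply is that Appendix 1 is inert. No section of the body calls on it, the decision route is the TSC's judgement under 2.1.5, and with no interim analysis planned the 5.5.1 clause cannot be triggered. That limits the practical harm. It does not remove the contradiction, because the appendix is part of the protocol and prescribes actions for each grade.

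Several stronger readings are tempting, and the documents do not support them:

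- *The study can never be graded Green.* The month-15 row could be Green against a target of 20 or 30.
- *It is certain to be Red at 12 months.* The 12-month point may fall after the study has ended. The printed cell also has a doubled conjunction, so a criterion may have been lost. A lost criterion could lift the grade to Amber but not to Green, since both printed criteria fail.
- *Red stops the study.* Table 1 asks for a review that considers closure; nothing is automatic.
- *Section 2.1.5 would let the randomised trial go ahead with an intervention that staff reject.* The section states a necessary condition, not a sufficient one. Section 1.2 and the synopsis rationale already require staff acceptability, and 7.2 plans interviews with healthcare professionals.
- *The study needs its own numeric traffic-light cut-offs.* For iterative, largely qualitative development in about 20 people, a judgement by the TSC is a defensible choice.

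**Conclusion.** The point holds as a contradiction within the current protocol. One row of Table 2 can never be assessed, one cannot do better than Amber, and one as printed can only give Red if it is reached. The fourth could be Green but has a horizon that does not suit this study. These results are the same for any sample size from 12 to 30 and rest only on one site and no control arm; the month-15 rates also depend on the assumed target and number recruited. The Section 7.3 reference is a plain error. The narrower wording of 2.1.5 is a minor misalignment, because other sections supply what it omits.

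**What to change.** 1. Remove Appendix 1 from this protocol and carry it to the protocol of the randomised trial.
2. Delete from 5.5.1 the reason that refers to an interim analysis in Section 7.3. The other reason listed there is unaffected.
3. As a minor alignment, word 2.1.5 to match 1.2 and 3.1, so that the TSC's recommendation to stop or proceed covers acceptability to patients and to healthcare professionals. The synopsis objective has the same patients-only wording and can be changed at the same time.

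This is an amendment of wording, with no new data and no more participants. Numeric cut-offs for the feasibility stage are optional and not needed to correct the error. If the TSC wants them, it should first check that the quantities are captured: same-day delivery of the first consultation, for example, is not in the data list of Section 3.2.
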